### 2.3. Sample size

From the 4 factors needed to calculate sample size (i.e., significance level, power, difference between groups, and standard deviation), 2 are unknown (difference between groups and standard deviation) because no previous study used HRV for older adults. Although pilot randomized controlled trials do not require sample size calculations, 15 to 20 participants per group would be necessary to ensure validity. Therefore, we will include 100 participants, 50 participants per group. Our results will provide the information necessary for sample size calculation in future studies.

### 2.4. Randomization

Participants will be randomly assigned to the exercise group (EG) (physical exercise protocol; EG) or the gametherapy group (GG) (gametherapy; GG). Simple randomization sequence will be obtained from randomization.com. Individual allocations will be sealed in an opaque and numbered envelope in sequential order in which participants will be drawn.

Group allocation will be revealed after we confirm that participant meets inclusion criteria, signs the consent form, and completes the initial assessment. All study-related information will be securely stored, and participants will be identified with a code to protect their identity. Records with names or other personal identifiers (i.e., address and informed consent forms) will be identified with a code, stored separately from study records, and accessible only by the research team.

### 2.5. Blinding

Due to the nature of the intervention, participants will be aware of the group they will be allocated to. However, researchers assessing primary and secondary outcomes will be blinded. Participants will be instructed not to disclose their allocation to the study team. Researchers analyzing the data will also be blinded.

### 2.6. Data collection

#### 2.6.1. Assessments plan.

Figure 2 represents the assessment data collection plan. Participants will be assessed in 4 moments: Assessment 1 at the beginning of the protocol, Assessment 2 after 24 sessions, Assessment 3 at the end of the wash-out phase (no intervention for 4 weeks), and Assessment 4 after 24 sessions (crossover phase or switch between protocols).

**Figure 2. F2:**
[figure not shown]
Data collection plan. 1RM = 1-repetition maximum test, 6MWT = 6-minute Walk Test, BBS = berg balance scale, CG = control group, EG = experimental group, FRT = functional reach test, GDLAM = Latin American group for maturity, HRV = heart rate variability, MMSE = mini-mental state examination, TUGT = timed up and go test.

#### 2.6.2. Data collection related to the primary aim (HRV) and (body composition).

HRV will be assessed at rest and during exercise using the Polar V800. The Polar V800 is a heart rate monitor that captures electrical impulses from the heart. A device similar to a watch will be placed on participants’ left wrist, and a chest strap with a capture sensor will be positioned on their xiphoid process.

The assessment at rest will describe participants’ cardiac autonomic profile. Participants will be quiet and rest in supine position for 20 minutes in an air-conditioned room (22°C–25°C).

The assessment during exercise will be completed in 2 moments: pre- and post-intervention. The cardiac responses to the different phases of the exercise (i.e., 5-minutes warm-up, 30-minutes aerobic training, 20-minutes strength training of peripheral muscles, and 5-minutes relaxation) will be observed. EG will complete a physical exercise protocol validated by Raimundo et al,^[8]^ and GG will perform gametherapy (Just Dance 2013) Marques et al.^[9]^

HRV will be measured at rest and during exercise using linear methods in the time and frequency domains, non-linear methods, and Poincaré graph. Data analysis will be based on the heart rate recorded during the protocol, and only time series with more than 95% of sinus beats will be used for analysis. After checking for errors, a trace will be selected for analysis and filtered using the Polar Precision Performance SW software (version 4.01.029). Analysis will be performed using the Kubios software.^[9]^

Body composition will be assessed using electrical bioimpedance. Participants will be fasting for 2 hours, with empty bladder (used the bathroom 30 minutes before), and will not have practiced physical activity in the previous 8 hours. OMRON equipment (model HBF-514) will be used; the equipment is composed of a tetrapolar system with 8 electrodes that transmit an extremely low electric current of 50 kHz and 500 µA. Six variables will be recorded: basal metabolism value, body fat percentage, skeletal muscle percentage, body mass index, visceral fat percentage, and basal metabolic rate.

#### 2.6.3. Data collection related to secondary outcomes.

##### 2.6.3.1. Assessment of respiratory pressures.

Respiratory muscle strength maximum inspiratory pressure and Maximum Expiratory Pressure will be measured using an analog manovacuometer (±150 cmH_2_O; Murenas). Manovacuometry is a simple, fast, noninvasive, and voluntary test requiring participants’ collaboration and maximum effort. Participants should be seated while the researcher is in front of them providing verbal encouragement. In addition to the manovacuometer, a chair, a nose clip, a flat mouthpiece, and a trachea will be needed for performing the test. For maximum expiratory pressure, participants will be asked to inflate their lungs to total lung capacity and perform a forced expiration, sustaining the peak pressure for approximately 5 seconds. For maximum inspiratory pressure, participants will be asked to exhale up to the functional residual capacity and perform a maximal inspiration, sustaining the pressure for approximately 5 seconds.^[10]^ Participants will perform 3 acceptable and reproducible maneuvers with a maximum difference of 10% among the values.

##### 2.6.3.2. Functional autonomy.

Functional autonomy will be assessed using the Latin American Group for Maturity (GDLAM) protocol. GDLAM comprises the simulation of 5 activities of daily living, namely walking 10 m, standing up from sitting position, standing up from prone position, standing up from a chair and moving around the house, and putting on and taking off a t-shirt. The following assessment tools will be used during the protocol: a stopwatch, a tape measure, a mattress, a 50 cm chair, 2 cones, and a t-shirt.^[11]^ The time in seconds to perform each simulation will be measured, and the GDLAM index of autonomy will be calculated in scores, in which lower values indicate higher functional autonomy.

We will also conduct the Functional Reach Test. This test measures the maximum distance an individual can reach forward by leaning the trunk with arms extended and shoulder in 90° flexion, without moving heels off the ground or touching the tape. Distances smaller than 15 cm indicate fragility and risk of falls, and values equal to or smaller than 17 cm indicate a 13-fold higher risk of falls.^[12]^

##### 2.6.3.3. Cognitive function.

The Mini-Mental State Examination will assess participants’ mental state and cognitive function. It is a 30-point questionnaire grouped into 7 categories that assess specific cognitive functions, namely orientation to time (5 points), orientation to place (5 points), registration (3 points), attention and calculation (5 points), recall of 3 words (3 points), language (8 points), and visual construction (1 point). Total score ranges from 0 to 30; The maximum score is 30. A score of 23 or lower indicates cognitive impairment. The cutoff is 19 for participants with low educational level.^[13]^

##### 2.6.3.4. Balance and risk of falls.

The Time Up and Go test will assess participants’ balance, functional mobility, and risk of falls. The test asks participants to get up from an armed chair, walk 3 m, turn around, walk back to the chair, and sit down. According to the time in seconds to complete the test, participants will be classified as without risk of falls (up to 10 seconds), partial dependence and low risk of falls (11–20 seconds), and significant deficit in physical mobility and high risk of falls (over 20 seconds).^[12]^

The Berg Balance Scale will assess participants’ risk of falls and functional dependence. The test consists of 14 predetermined tasks that are common to daily living, each of which is scored on a scale from 0 to 4. The score is based on the time required to perform and maintain a position, perform a task, or reach a distance with the upper limb. The maximum score is 56; higher scores indicate better balance. Scores equal to or lower than 36 are associated with a 100% risk of fall.^[14]^

##### 2.6.3.5. Functional capacity.

The 6-minute walk test will assess participants’ functional exercise capacity and general respiratory, cardiac, and metabolic functioning. The test consists of walking at maximum and constant speed along a 30 m corridor. Cones will indicate the distance to be covered, and each meter will be marked on the floor with yellow tape. Participants will be verbally encouraged to maintain their walking speed (e.g., “You are walking very well; keep it up!” “Keep the rhythm”). The distance covered in meters will be compared with reference values for the Brazilian population.^[9]^

### 2.7. Intervention

#### 2.7.1. Exercise group.

EG will perform an exercise protocol composed of aerobic and strength exercises validated by Raimundo et al.^[8]^ The exercise protocol comprises 24 sessions of 60 minutes each and will last 12 weeks. Each session will start with a 5-minute static stretching of forearm and leg flexors and extensors, and arm abductors. Then, it will be followed by a 30-minute walk on a treadmill. During the walk, participants’ heart rate will be monitored to keep between 50% and 70% of their heart rate reserve.^[15]^ Participants will perform 20 minutes of strength exercises at 50% to 70% of their 1-repetition maximum. Strength exercises will comprise 3 sets of 10 repetitions of muscular resistance exercises for forearm and leg flexors and extensors, and arm abductors. A 5-minute deceleration exercise will be performed at the end of the session. Participants will perform 2 sets of 10 repetitions of diaphragmatic breathing in dorsal decubitus or sitting position. Vital signs (i.e., blood pressure, heart rate, respiratory rate, and oxygen saturation) will be measured before and after each session.

Training will be individual and take place at the Institute of Tisiology and Pneumology of Campina Grande, Paraíba ([name] [name], CNPJ:088529880001-64, [name]), in the physical therapy service. The exercise protocol will be performed exclusively after the institutional authorization term, and a researcher with degree in physical therapy will supervise all sessions.

##### 2.7.1.1. Adherence to the exercise protocol.

Attendance to sessions will be registered, and the percentage of attendance will be calculated. The punctuality, engagement in other physical activities in addition to the protocol, number and type of adverse events, and adherence attitude during the session will also be registered. The level of perceived exertion, mood, and feeling of acute exhaustion induced by exercise will be recorded to anticipate possible fatigue symptoms or dissatisfaction and allow proper adjustments in the protocol. Adherence is essential to investigating the effectiveness of the exercise protocol; therefore, strategies will be implemented to maximize it (e.g., sending motivational messages every week and videos every month via WhatsApp).

#### 2.7.2. Control or GG.

Participants will play Just Dance (2011), a game-based therapy in which participants should follow dance movements. All movements will be tracked through the Kinect sensor to quantify performance at the end of the session. Xbox 360º device with Kinect (4 Gb; Microsoft) will be connected to a TV with compatible video formats. Participants will exercise for 60 minutes without interruption, and their heart rate will be monitored with an oximeter. Their heart rate should be between 50% and 70% of the heart rate reserve.^[15]^

### 2.8. Crossover

The first phase of the study should be carried out in 14 weeks, that is, 2 weeks of assessments (Assessment 1) and 12 weeks of intervention. After EG AND CG INTERVENTION OR INTERVENTION A, participants will be reassessed (Assessment 2). All this process may last 15 weeks. In the wash-out phase, participants will not receive any interventions for 4 weeks. Around the 20^th^ week, participants will return for assessment 3, and EG and CG will switch protocols. After the crossover phase, all participants will be reassessed (Assessment 4).

### 2.9. Follow-up

During the follow-up, all participants will receive the same treatment (i.e., regular standard care), which will allow the assessment of the medium-term effects of the exercise and gametherapy protocol.

### 2.10. Participant safety

Any adverse effects (i.e., any musculoskeletal injury that occurs during or because of the training) will be reported.

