### 3.1. Limitations/study risks and contingency plan

Potential risk 1: EG participants not attending to intervention sessions.

Contingency plan: Different strategies will be implemented to maximize adherence to the exercise protocol. The emotional state (The Feeling Scale) will be monitored, and any adverse events will be registered during training to understand participants’ feelings and implement adaptations. Participants will also receive motivational messages via WhatsApp every week and motivational videos from coaches and the research team at the beginning of each month.

Potential risk 2: Low recruitment and/or retention rate.

Contingency plan: The research team will invite as many active older adults to participate as possible. If the recruitment rate is still low, we will reach out to other exercise training facilities in different areas to recruit potential participants.

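### Section 2.10 makes only musculoskeletal injury reportable although the plan registers adverse events of any type, and the wider log, attendance record and motivational support are stated for the exercise group only

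*Protocol article*

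**What the plan says.** The trial-wide safety rule is a single sentence in section 2.10: "Any adverse effects (i.e., any musculoskeletal injury that occurs during or because of the training) will be reported". It is not tied to an arm.

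Two other places use a wider idea of an adverse event. Section 2.7.1.1 lists, among the items kept for each participant, "number and type of adverse events, and adherence attitude during the session will also be registered". Section 3.1 says that "any adverse events will be registered during training". Neither restricts the type of event.

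Section 2.7.1.1 is a subsection of 2.7.1 (Exercise group) and is titled "2.7.1.1. Adherence to the exercise protocol". It also holds the attendance rule, "Attendance to sessions will be registered, and the percentage of attendance will be calculated", the recording of exertion, mood and exhaustion, and the support measures, for example "sending motivational messages every week and videos every month via WhatsApp". Section 3.1 presents the same support and event registration as the answer to a risk that names one arm: "Potential risk 1: EG participants not attending to intervention sessions".

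Section 2.7.2, on GG, describes the game, the motion-sensor equipment, the session length and the target heart rate. On monitoring it says: "Participants will exercise for 60 minutes without interruption, and their heart rate will be monitored with an oximeter". It states no attendance record, event log or motivational contact.

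**The concern.** Two things are at stake.

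The first is what gets reported. Participants are aged 60 to 80, and controlled chronic disease is allowed (section 2.2.2). Both arms train at a set share of heart rate reserve (sections 2.7.1 and 2.7.2), and risk of falls is a secondary outcome. The events a reader would most want to see, such as a cardiovascular event, a syncope or a fall without injury, lie outside the wording of section 2.10. So does anything that happens during an assessment, because the rule covers only events during or caused by training. The assessments include maximal respiratory efforts and a walking test at maximum speed (sections 2.6.3.1 and 2.6.3.5).

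The second is comparability. If all-type event recording belongs to one intervention only, event counts by arm reflect how hard each arm was watched as well as how safe it was. If weekly messages and monthly videos go with one intervention only, their effect is mixed into the EG-GG contrast.

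**Working it through.** The plan gives no figure to reproduce here. The check is a comparison of texts, followed by a count of exposure.

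**1. Which events are registered, and which must be reported**

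| Event | EG: registered? | GG: registered? | Must be reported under 2.10? |
|---|---|---|---|
| Musculoskeletal injury during or because of training | Yes (2.7.1.1, 3.1, 2.10) | Yes, through 2.10 | Yes, both arms |
| Cardiovascular event, syncope or non-injurious fall in a session | Yes (2.7.1.1, 3.1) | Not stated | No, either arm |
| Any event that ends participation | Could surface as a drop-out reason (2.11) | Same | Only as a drop-out reason |

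The second row contains both problems. The gap in reporting affects both arms. The gap in recording affects GG.

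**2. What a safety table would look like**

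- If the report follows section 2.10, both arms show musculoskeletal injury only, and other events logged in EG are left out.
- If the report follows the session log, EG shows all event types and GG shows musculoskeletal injury only. EG then looks worse on the remaining types simply because it was asked.

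Neither table supports a fair all-type comparison.

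**3. Does the crossover remove the difference in support?**

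Let E and G be the effects of the exercise and game protocols, and m the effect of the messages and videos, given only with the exercise protocol. Section 2.8 has the arms switch protocols after wash-out.

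- Period 1 contrast: (E + m) − G
- Period 2 contrast: (E + m) − G
- Average over periods: (E − G) + m

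The support follows the protocol and not the person, so m does not cancel. The documents give no basis for its size.

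**4. Exposure count**

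Inputs: 100 participants (section 2.3), assessments after 24 sessions in each period (section 2.6.1), and 2 periods (section 2.8).

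- Planned sessions: 100 × 24 × 2 = 4,800
- GG sessions, one GG period per participant: 100 × 24 × 1 = 2,400
- Share: 2,400 / 4,800 = 50%
- Period 1 alone, at 50 per group: 50 × 24 = 1,200 of 2,400

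The overall 2,400 does not depend on an even split, because every participant has one GG period. It does assume full attendance, no drop-out and 24 GG sessions per period; section 2.7.2 gives no session count of its own.

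Over a 12-week exercise period, weekly messages and monthly videos come to about 12 messages and 3 videos per participant.

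**The case against.** A fair defence has four parts.

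- **Loose wording.** The article uses the same abbreviation loosely elsewhere. In section 2.4 it introduces what can only be examples of personal identifiers, and in the Introduction it glosses body composition with a list that differs from the six variables in section 2.6.2. Section 2.10 may be careless and not a deliberate exclusion. This stands as an explanation, but the sentence still reads as a definition and conflicts with sections 2.7.1.1 and 3.1.
- **Other safeguards.** A reader might infer that cardiac events and falls are not counted at all. The documents do not support that. In EG, session events of any type are registered. Musculoskeletal injury is reportable in both arms. Drop-out reasons (section 2.11) and withdrawals by the research team (section 2.11.2) carry no arm restriction. These safeguards are partial: they catch only events that end participation, and section 2.11.1 lets participants leave without giving a reason.
- **Silence about GG.** A reader might also infer that GG attendance goes unrecorded, that GG gets no messages, or that the dose received cannot be compared. That turns the silence of a short paragraph in a condensed article into a statement. Section 2.6.1 times assessments by session count without separating the arms, which presupposes some counting in both, and section 2.7.2 measures game performance and heart rate. This limits the point to what happens if the text is followed literally. It does not remove it, because placement under the EG heading and the naming of EG in section 3.1 are positive text.
- **No size of bias.** The count of 2,400 sessions measures exposure. It does not estimate events missed or bias in any outcome. This stands in full.

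**Conclusion.** The point holds in two parts of unequal strength.

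The firmer part is a contradiction. The reporting rule in section 2.10 is narrower than the registration described in sections 2.7.1.1 and 3.1, so an EG event that is not musculoskeletal can be logged and need not be reported. This rests on stated text alone.

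The second part is conditional. If the article is followed literally, all-type event logging, attendance recording and motivational contact accompany the exercise protocol and not the game protocol, in both periods. Up to 2,400 of 4,800 planned sessions would then lack a stated all-type event log or attendance record, on the assumptions of full attendance and 24 GG sessions per period. If the team already treats both arms alike, only the wording needs to change. The documents do not show that serious events go uncounted everywhere or that GG is denied support, and they do not show how large any bias would be.

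**What to change.** 1. Reconcile section 2.10 with sections 2.7.1.1 and 3.1. Use one definition covering adverse events of any type, naming falls, cardiovascular events and syncope alongside musculoskeletal injury, and covering events during sessions or assessments and those reported at visits.
2. Record these events on the same form in both arms, and report them by intervention and by period.
3. State that section 2.7.1.1 and the first contingency plan in section 3.1 apply equally to EG and GG: attendance, session log, messages and videos.

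The cost is modest: revised wording, one log sheet used in both arms, and the same messages sent during GG periods. Active collection of every event from consent to Assessment 4 would cost more. Section 2.8 gives 15 + 4 = 19 weeks to the end of wash-out, and a second 12-week period would bring this to 31 weeks plus assessment time, so follow-up between visits would be needed. The change above does not require that.

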### 2.11. Participant drop out

We will record and inform the number of participants that drop out of the study and the reason.

#### 2.11.1. Participant abandonment.

Participation in this study is entirely voluntary. Participants can leave the study at any time without explaining. Leaving the study will not result in any negative consequences regarding care or treatment received.

#### 2.11.2. Interruption of the intervention by the research team.

The research team may withdraw participants at any time if their safety is at risk or the study protocol is violated, which may occur under the following circumstances:

- Severe musculoskeletal injuries that alter their usual lifestyle (whether or not as a consequence of the study participation).

- Change of residence, hindering the assessments.

- Death.

### 2.12. Statistical analysis

Baseline measures between groups will be compared. The distribution of continuous quantitative variables will be tested for normality and graphically inspected using histograms. A general linear model will analyze differences between groups for the primary and secondary outcomes. If normality assumption is not met, we will proceed with non-parametric techniques (i.e., quantile regression). Effect size (95% confidence interval) and level of statistical significance will be displayed. Missing data will be replaced using multiple imputations. We will minimize potential confounding by adjusting baseline values and controlling other potential confounders. Statistical significance will be set at *P* < .05.

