**Method::**

This randomized clinical trial will include 100 active older adults aged 60 to 80 years. The exercise group (EG) will perform 24 supervised training sessions (strength and aerobic) for 12 weeks (2 60-minutes sessions per week). The gametherapy group (GG) will exercise using gametherapy. Assessments will occur on the first week, after the 12th week, after wash out and in the end of cross over. The primary outcome will be HRV and body composition (bioimpedance). Secondary outcomes will be functional capacity (6-minute walk test), cognitive function (mini-mental state examination), risk of falls and balance (berg balance scale and timed up and go test), inspiratory and expiratory pressures (manovacuometry) and functional autonomy (functional reach test and group of Latin American development to maturity [GDLAM] protocol).

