## 2. Material and Methods

### 2.1. Study design and protocol registration

This is a parallel-group randomized clinical trial registered at REBEC (Clinical Trial registration # RBR-7y24t7t). The research protocol was reviewed and approved by the research ethics committee of Centro de Ensino Superior e Desenvolvimento da Paraíba (#4462499 - CAAE: 39751620.0.0000.5175).

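### The trial is labelled parallel-group but run as a two-period crossover, and the stated between-group model does not fit the data collected after the switch

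*Protocol article*

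**What the plan says.** On design, section 2.1 of the protocol article reads "This is a parallel-group randomized clinical trial registered at REBEC". The Abstract gives a different schedule: "Assessments will occur on the first week, after the 12th week, after wash out and in the end of cross over". Section 2.8 (Crossover) confirms it. After the first intervention period, "In the wash-out phase, participants will not receive any interventions for 4 weeks", and then "participants will return for assessment 3, and EG and CG will switch protocols". CG there is the gametherapy group (GG), as the heading of 2.7.2 shows. Section 2.6.1 places Assessment 4 after a further 24 sessions, once the programmes have been exchanged. On the length of a period, section 2.7.1 says "The exercise protocol comprises 24 sessions of 60 minutes each and will last 12 weeks", and section 2.8 also counts 12 weeks of intervention in the first phase.

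On analysis, section 2.12 says "A general linear model will analyze differences between groups for the primary and secondary outcomes", with quantile regression if normality fails, and with adjustment for baseline values and other possible confounders. It does not mention the crossover, and it does not say how data collected after the switch enter the analysis. Section 2.3 sizes the trial as 100 participants, 50 per group, and makes no use of the crossover.

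**The concern.** The design label and the design as run contradict each other, and nothing else in the article reconciles them. The label matters because the analysis sentence depends on it. In a parallel-group trial, group and treatment are the same thing throughout. In this trial they are the same at Assessment 2 and opposite at Assessment 4. Each participant also contributes to both assessments, so those observations are correlated.

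At stake is what a reader may conclude from the second half of the trial. Depending on how the sentence in 2.12 is applied to the post-switch data, a real difference could appear with its sign reversed, disappear, or carry a wrong standard error. If the reading is not fixed beforehand, it can be chosen after the results are known.

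**Working it through.** **Inputs from the protocol article.** Two groups of 50 (2.3); Assessments 1 to 4, with the swap between Assessments 3 and 4 (2.6.1, 2.8); significance at 0.05 (2.12), taken here as two-sided.

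**Inputs assumed.** Section 2.3 says the group difference and the standard deviation are unknown. Results are therefore in SD units, with a true EG minus GG difference of 0.5 SD in the simulation and 0.3 SD in the power illustration. The within-person correlation rho is 0.375 to 0.6 in the formulas and 0.5 or 0.7 in the simulation. The period effect is 0.2 SD. The sample size in 2.3 rests on no stated difference, SD or power, so there is no figure of the plan's own to reproduce here.

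**Step 1: what randomised group estimates.** Let t be the EG minus GG effect, p the period effect and m the mean under GG in period 1, with no carry-over.

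| Sequence | Assessment 2 | Assessment 4 |
|---|---|---|
| EG then GG | m + t | m + p |
| GG then EG | m | m + p + t |
| Difference, first row minus second | t | -t |

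The average of the two differences is (t - t)/2 = 0. The reversal and the cancellation do not depend on the size of t, p or rho.

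**Step 2: standard errors.** With 100 participants and unit SD:

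- Pooled by treatment received, rows taken as independent: sqrt(2/100) = 0.141.
- Paired (within participant): sqrt(2(1-rho)/100) = 0.112 at rho 0.375 and 0.089 at rho 0.6.
- Ratio: 1/sqrt(1-rho) = 1.26 and 1.58.
- Pooled by randomised group, true SE: sqrt((1+rho)/50) = 0.173 at rho 0.5. The independent-rows value under no effect is 0.141, so here the model SE is too small.
- Assessment 2 adjusted for Assessment 1, 50 per group, same rho assumed between those two assessments: 0.20 x sqrt(1-rho²) = 0.185 at rho 0.375 and 0.16 at rho 0.6.

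**Step 3: simulation.** 2,000 trials per scenario, 50 per sequence, true difference 0.5 SD, no carry-over, no baseline covariate, period term in the pooled models, rho 0.5. The last column uses separate runs with no true difference.

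| Analysis | Mean estimate | Empirical SE | Model SE | Rejections under no effect |
|---|---|---|---|---|
| Group at Assessment 2 | 0.504 | 0.201 | 0.199 | 0.052 |
| Group at Assessment 4 | -0.502 | 0.200 | 0.200 | 0.052 |
| Group, Assessments 2 and 4 pooled | 0.001 | 0.173 | 0.146 | 0.111 |
| Treatment received, rows independent | 0.503 | 0.101 | 0.141 | 0.006 |
| Paired crossover analysis | 0.503 | 0.101 | 0.099 | 0.049 |

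At rho 0.7 the pattern is the same. Rejections under no effect are 0.140 for the pooled group analysis and 0.001 for treatment received with independent rows.

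**Step 4: power for an assumed 0.3 SD.**

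- Paired: Phi(0.3/SE - 1.96) = 77% at rho 0.375 and 92% at rho 0.6.
- Treatment received, rows independent: Phi((0.3 - 1.96 x 0.141)/true SE) = 58% and 60%.
- Assessment 2 adjusted for Assessment 1: Phi(0.3/0.185 - 1.96) = 37% and Phi(0.3/0.16 - 1.96) = 47%.

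**Step 5: carry-over, if any.** If a fraction c of the first-period difference persists to Assessment 4, the paired estimate becomes t(1 - c/2). For c = 0.25 and 0.5 with t = 0.5, this is 0.44 and 0.375; simulation at rho 0.7 gave 0.440 and 0.374. The paired model does not remove carry-over.

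**The case against.** The strongest reply is that section 2.12 is silent, not wrong. A general linear model can hold period and repeated-measures terms, this is a condensed article, and an unseen analysis plan may supply them. That stands as far as model terms go. A reader might infer that the plan excludes period and participant effects, but the text does not say so, and leaving them unnamed is no fault in itself. What remains is the design label in 2.1, which contradicts 2.8, and a contrast that is defined by group in a trial where the groups exchange treatments.

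Second, a reader might infer that the primary analysis, followed as written, returns zero or the wrong sign. The document does not support that. Taken with the parallel-group label, section 2.12 most naturally means a baseline-adjusted comparison after the first period, which is valid. Reversal or cancellation needs an analyst to keep the original group label after the swap, and nothing prescribes that.

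Third, a reader might infer that carry-over is present because the wash-out is a third as long as the training. The ratio shows nothing about persistence, and a wash-out and an Assessment 3 are both planned.

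Fourth, precision is no argument for making Assessment 2 primary. Its SE exceeds even the 0.141 of the independent-rows analysis, which is merely conservative. That is correct, so the choice of primary is a trade-off.

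Finally, section 2.3 speaks of the trial partly in pilot terms. That lowers the weight of any confirmatory claim, but it does not reconcile the sections.

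**Conclusion.** The point holds in a limited form. Section 2.1 contradicts the Abstract, 2.6.1 and 2.8 on the design, and the contrast in 2.12 does not fit the post-switch data. The Assessment 2 comparison is unaffected.

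For analyses that use Assessment 4, the sign reversal and the cancellation follow from the design alone when there is no carry-over. The standard-error ratio of 1.26 to 1.58 rests on an assumed rho of 0.375 to 0.6. The power and carry-over figures rest on assumed effect sizes and fractions that the article does not give, so they are illustrations only. Carry-over remains a possibility that the document neither shows nor rules out.

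**What to change.** In 2.1, describe the trial as a randomised two-period, two-sequence crossover (EG then GG, GG then EG).

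In 2.12, make three statements:

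- Any analysis that uses Assessment 4 is a linear mixed model with treatment received, period and sequence as fixed effects and participant as random effect.
- Either that model or the comparison at Assessment 2 adjusted for Assessment 1 is primary, and the choice is made before data are seen.
- The difference between sequences at Assessment 3 is reported descriptively. It is not a pre-test that selects the analysis.

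The cost is wording only; no visit, programme or wash-out changes. The choice of primary has its own price. The Assessment 2 comparison avoids carry-over, but its SE is about 0.16 to 0.185 SD against 0.089 to 0.112 SD for the paired analysis at the same assumed correlations, so its interval is roughly 1.7 to 1.8 times as wide (0.185/0.112 and 0.16/0.089). The mixed model gains that precision but relies on carry-over being negligible.
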